### Treatment as usual

2.7.

TAU comprises all the routine care that an individual receives when they present their symptoms at the primary or student health service or occupational health services unit (corresponds to primary care-level treatment) or another unit that recommends the study to the participant. Both the intervention arm and TAU arm participants will receive usual care, but TAU will be enhanced by the study intervention in the intervention arm. In practice, TAU may vary among the study participants based on their individual needs, for example, treatments for comorbid somatic diseases or psychiatric disorders with which this study will not interfere.

In addition to TAU, all the participants will be given a self-help and educational leaflet based on scientific knowledge related to their condition. This leaflet includes a short description of the health conditions and an explanatory description of the biopsychosocial perpetuating mechanisms of PPS. The leaflet also outlines self-help principles for participants (Table 3).

**Table 3 tab3:** Description of educational leaflet for study participants.

Contents	PPS related to indoor air	Chronic fatigue
Specific contents	- Description of multi-organ symptom profile and three main categories of IA-related symptoms (i) complaint reactions due to poor subjective IA, (ii) disease or building-related illness that may be caused by IA factors and (iii) PPS with an unclear cause but with a possible relation to IA*) - Main principles of managing symptoms associated with IA - Factors related to build environment, psychosocial and personal factors associated with IA symptoms	- Description of core symptoms, multi-organ symptom profile, and differential diagnosis related to situational fatigue - Main principles of managing chronic fatigue and its consequences for an individual’s life (i) accepting the condition, (ii) understanding one’s role in symptom management, (iii) recognizing the predisposing and perpetuating factors of the symptoms, and iv) working on the cognitions and emotions that might increase the symptom burden)
Common contents	- Interaction of biopsychosocial factors that influence PPS - Automatic central nervous system reactions, “flight or fight” mechanism - Healthcare treatment for PPS based on individual assessment - Reactive psychological distress associated with PPS - Principles for self-help and symptom management	

* The focus of this study.

IA, indoor air; PPS, persistent physical symptoms.

### Outcomes

2.8.

The primary outcome of this study is health-related quality of life (HRQoL) measured by the 15D questionnaire (Sintonen, 2001; Sintonen, 2013). The 15D is a utility-based generic, standardized measure, comprising the following 15 dimensions that describe physical, mental, and social wellbeing: mobility, vision, hearing, breathing, sleeping, eating, speech, excretion, usual activities, mental function, discomfort and symptoms, depression, distress, vitality, and sexual activity. Each dimension is graded by the respondent on a scale ranging between 1 (no perceived problems at all) and 5 (severe problems). Thus, the 15D can be used to measure a vast number of health states. We will use the 15D data to derive 15D overall scores with values from 1 (full health) to 0 (being dead), as well as to obtain dimensional symptom profiles. We will also measure secondary outcomes such as condition-specific outcomes (fatigue or symptoms related to various environmental factors), daily functioning (e.g., occupational, social, and cognitive functioning), cognitive and emotional functioning and psychiatric symptoms, and treatment satisfaction and changes that are experienced as negative by the participants related to the intervention (Table 4). We will also collect demographics and background information. Table 4 shows the description of the measurements and chronology of the assessments. The set of outcomes follows the recommendations of the European expert network of clinicians and researchers on persistent somatic symptoms (EURONET-SOMA) designed to harmonize core outcome domains in clinical trials on PPS (Rief et al., 2017). A random sample of volunteer participants will be interviewed at the end of the trial considering the treatment to gather qualitative data about treatment usability and acceptance.

**Table 4 tab4:** Outcomes and their assessment time schedule.

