Treating PPS has been challenging because of both the ambiguous definition of the condition and the divergent views of patients and clinicians on the mechanisms of the condition. These discrepancies are reflected in the acceptance of treatment modalities and the aims of treatments, resulting in frustration and feelings of being misunderstood among both patients and professionals (Olde Hartman et al., 2009; Peters et al., 2009; van Ravenzwaaij et al., 2010; Adamowicz et al., 2014; Pemberton and Cox, 2014; Tuuminen et al., 2016; Vuokko et al., 2016). Psychosocial, patient-involving methods, such as cognitive-behavioral psychotherapy (CBT), which support individuals’ abilities to manage their symptoms and health behaviors, have shown promising effects in supporting the functional ability and quality of life of individuals with PPS (Henningsen et al., 2018). However, the effect sizes have remained rather moderate and the information on factors explaining the variability of individuals´ responses to treatment is scarce (Kleinstauber et al., 2011; van Dessel et al., 2014). It has also been suggested that the rationale behind the psychosocial treatments remains unclear for the patients and thus results in unwanted effects such as withdrawal from the treatment (Geraghty and Scott, 2020). To respond to these challenges some studies have suggested that tailoring treatments according to personalized profiles might improve the effectiveness (Rosmalen et al., 2020; Senger et al., 2021a,b). These profiles include both state characteristics such as the severity of the symptoms and comorbidities but also lifestyle factors and cognitions and emotions that contribute to the response to treatment. If aiming to improve personalization, these characteristics should be evaluated when referring to the treatment. The acceptability of these treatments among symptomatic individuals is also low—presumably because of the stigma related to psychological treatments and the vague definition of the condition (Åsbring and Närvänen, 2002; Looper and Kirmayer, 2004; Dickson et al., 2007; Finell et al., 2018). As adherence is suggested to improve the treatment effect on health even more than improvements in specific treatments methods (Brown and Bussell, 2011; Donkin et al., 2011), more information on the tools for increasing personalized approaches and rationale for treatments and acceptability for patients is urgently needed to improve clinical practices and to enhance patients’ functioning.

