**Treatment satisfaction, adverse effects, and usage**						
*Working Alliance Inventory (Horvath and Greenberg, 1989)		X	X	X		
Treatment satisfaction (Seligman, 1995)		X	X	X		
Interview of treatment acceptance						X
Engagement to intervention: total number of logins and time during web-based program, modules, and exercises completed						
Reasons for discontinuing						

BL, questionnaire before recruitment interview; 0 W, questionnaire after recruitment clinical interview; 6 W, questionnaire 6 weeks after beginning of eHealth intervention; 14 W, questionnaire 14 weeks after 0 W questionnaire; 6, questionnaire 6 months after 0 W questionnaire; 12, questionnaire 12 months after 0 W questionnaire.

* In the eHealth intervention arm, the participants fill in the Working Alliance Inventory (WAI) for4 weeks from the beginning of the web-based program and after the last module.

** Scales will be used as a base for assessing disability related to the symptoms in recruitment interview.

In addition, we will ask for the participants’ permission to use and combine the registered information of the health check-up data with the study data. The Finnish national health registers will be used to collect data on outpatient visits (AvoHILMO data), data on inpatient care (HILMO data), and data on occupational health service use, and to collect information on prescribed and reimbursed prescription medicine purchases, rights for special reimbursement for medicines, and information on sickness and disability benefits and rehabilitation with diagnoses. This information will be used to assess the effectiveness of the rehabilitation program in reducing the burden of healthcare services and the social security system.

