### Monitoring

2.14.

This study will be monitored by the steering group every 6 months. The steering group will evaluate recruitment proceedings and data management and if necessary, propose changes to the protocol (amendments before submission of this protocol are reported in this manuscript). The approval of the ethics committee will be requested in any case of a change of study protocol and the ClinicalTrials.gov registry will be informed. All the authors will be given access to the cleaned data sets. Generally, no harms are reported during psychotherapeutic interventions (van Dessel et al., 2014) and no side effects or serious risks have been reported from participating in eHealth interventions based on case formulation and ACT programs. However, if any should occur during the treatment, the participants will be offered individual counseling from medical professionals (AV, TP), and will be referred for relevant treatment elsewhere if considered appropriate. To control the possibility of harm, our study participants will also remain in their usual care during the eHealth intervention to prevent any possible unwanted effects during the web-based program. Any adverse effects reported by the participants will be recorded and reported in the trial publications. As we expect no harm related to the intervention, no separate data monitoring group will be considered. Neither will further auditing procedures of the trial be considered.

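### Section 2.8 refers to Table 4 for the measurement of negative changes, but the table has no instrument or time point for them, so the promised harm reporting has no control rate

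*Protocol article*

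**What the plan says.** Three places in the protocol article bear on harms.

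- **Section 2.8 (Outcomes)** includes among the secondary outcomes "changes that are experienced as negative by the participants related to the intervention (Table 4"). It adds: "Table 4 shows the description of the measurements and chronology of the assessments". A reader should therefore find both the instrument and its timing in that table.
- **Table 4** has a block headed "Treatment satisfaction, adverse effects, and usage". Its rows are the Working Alliance Inventory, treatment satisfaction, "Interview of treatment acceptance", engagement with the program, and "Reasons for discontinuing".
- **Section 2.14 (Monitoring)** states: "Any adverse effects reported by the participants will be recorded and reported in the trial publications". It gives no method of asking, no schedule and no procedure by arm.

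The Introduction mentions a suggestion in the literature that an unclear rationale for psychosocial treatment "results in unwanted effects such as withdrawal from the treatment".

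**The concern.** A declared outcome has no stated means of measurement. The article promises to publish adverse effects, but the only collection method it describes is recording what participants report.

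Two features limit what such a record can show. The outcome concerns effects of the intervention, so usual-care participants cannot supply a comparison rate. The arms also differ, by design, in how often a participant is in touch with someone to whom a bad experience could be mentioned. A low count could mean few harms or little asking. A higher count in the intervention arm could mean more harm or more opportunity to report it.

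**Working it through.** **1. Table 4 against section 2.8.** Rows under the heading that names adverse effects:

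| Row | Time marks | Could it serve as the negative-change measure? |
|---|---|---|
| Working Alliance Inventory | 0, 6 and 14 weeks | No. It measures alliance, and the footnote ties it to the intervention arm |
| Treatment satisfaction | 0, 6 and 14 weeks | Only indirectly; nothing at 6 or 12 months |
| Acceptance interview | 12 months | Only in part. Section 2.8 says "A random sample of volunteer participants will be interviewed at the end of the trial", on usability and acceptance |
| Engagement | none | No. It records program usage |
| Reasons for discontinuing | none | Only for those who stop |

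No row in the other blocks (primary outcome, background, symptoms, cognitive and emotional functioning, occupational functioning) is a negative-change measure either. The cross-reference from section 2.8 leads to a heading with nothing beneath it for this outcome.

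**2. Opportunity to report, by arm.** Section 2.6 gives the intervention arm two psychologist sessions, one therapist call and written feedback on ten modules: 2 + 1 + 10 = 13 scheduled contacts, plus an open message channel. Section 2.7 describes usual care as routine care. Beyond the allocation call and email that both arms receive (section 2.10), the article describes no study contact for usual-care participants other than questionnaires.

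**3. What a zero count would show.** The article states no harm rate, so there is no figure to reproduce. For zero events among n patients with every event captured, the exact one-sided 95% upper bound is 1 − 0.05^(1/n). Section 2.12 gives more than one possible n: 62 per arm from the power calculation, and 50 per arm from the statement that 100 are randomized.

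- n = 62: 1 − 0.05^(1/62) = 0.0472, about 4.7%
- n = 50: 1 − 0.05^(1/50) = 0.0582, about 5.8%
- n = 100, if the planned 200 were all randomized: 1 − 0.05^(1/100) = 0.0295, about 3.0%

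If only a fraction c of events is reported, the bound on the true rate is divided by c. With an assumed c of 0.5, 4.7% becomes 9.4% and 5.8% becomes 11.6%.

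**4. Effect of unequal capture.** If the true rate p is the same in both arms and the capture fractions are c₁ (intervention) and c₀ (usual care), the apparent risk ratio is (p × c₁)/(p × c₀) = c₁/c₀, whatever p is. The article gives no capture fractions. Assuming 0.8 against 0.4 gives 2, 0.8 against 0.2 gives 4, and equal capture gives 1. These values show only the mechanism and do not estimate the bias in this trial.

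**The case against.** The case on the other side is substantial, and much of it stands.

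- **Worsening is observable.** A reader might infer that deterioration will be missed. The article does not support that. 15D is scheduled at all six time points. PHQ-9, PHQ-15, GAD-7, ISI, work ability and daily functioning are scheduled at baseline, 14 weeks, 6 months and 12 months, with no arm restriction stated. What is absent is a stated summary of worsening.
- **No between-arm harm test is announced.** Neither section 2.13 nor section 2.14 plans one, and restricting the outcome to effects of the intervention is a choice of definition. The ascertainment concern therefore applies only if someone compares the counts.
- **The source of reports is not stated.** A reader might infer that reports will come mainly from the intervention arm and that the harm result will be unreliable. Unequal contact makes this plausible, but no section says so. Section 2.10 says therapists are not explicitly told which patients come from the study, and no route from therapist to trial record is described. On the other hand, the psychologists who give the two sessions are the study researchers who also inform participants of their allocation.
- **The expectation of no harm** is given in section 2.14 as the reason for having no data monitoring group. It is not offered as the reason for the method of collecting harms.
- **The Introduction** reports a suggestion, and its one example is withdrawal, for which Table 4 has a row.
- **An article condenses.** Item wording may sit in a fuller document, and a row lost from the table cannot be wholly excluded. But section 2.8 itself says the measure and its timing are in Table 4, so the mismatch lies within the article.
- **The zero-event bound** is a property of sample size, and better questions would not change it. It limits what silence can mean but is not evidence of bias.

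**Conclusion.** The point holds in limited form. Section 2.8 declares an outcome and refers to Table 4, where no row, instrument or time point measures it, and section 2.14 falls back on participant reports. As written, harm reporting has no control rate, and a comparison of counts between arms would be open to unequal ascertainment of unknown size. A record of no reports would exclude only rates above about 4.7% (62 per arm) or 5.8% (50 per arm), assuming every event is captured; with incomplete capture the bound is higher.

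The primary analysis of 15D is unaffected. This is an inexpensive improvement to harm reporting. It does not show that the harm result will be wrong.

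**What to change.** 1. Add the same few neutrally worded negative-change items, not restricted to the intervention, to the existing 14-week, 6-month and 12-month web questionnaires in both arms. Report the answers by arm with denominators.
2. State that visits completed before the change lack these items. Section 2.9 puts recruitment at August 2020 to June 2022 with 12 months of follow-up, so coverage may be partial. If collection has already ended, say instead what was asked, in which arm and when.
3. Report by arm, as a descriptive summary, the share whose 15D worsens by at least 0.015, naming the reference questionnaire. Section 2.12 gives 0.015 as the minimally important change between arms; using it as an individual cutoff is a choice made here and should be labelled so. Some participants will cross it through ordinary fluctuation, so the contrast with usual care is the informative part.
4. Make sections 2.8 and 2.14 and Table 4 agree: either give the negative-change measure its own row with time points, or remove the reference to Table 4 and state how reports are elicited in each arm.

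**Cost:** slight extra questionnaire burden and one more table. The 15D summary needs no new data.

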### Objectives

1.1.

The aim of this randomized controlled trial (RCT) is to investigate the effectiveness of individual case formulation by using a functional case conceptualization method and shared goal-setting for the treatment, combined with an ACT web-based program, in comparison to treatment as usual (TAU) for disabling PPS among individuals with PPS related to i) indoor environments or ii) chronic fatigue syndrome. Its´ secondary aims are to assess the interaction of individual reaction patterns and processes based on the theoretical model of psychological flexibility with the intervention’s effectiveness and to investigate whether the intervention decreases participants’ overall symptom burden and improves daily functioning. We will also explore the participants’ adherence and response to the treatment to increase our understanding of the acceptability of the interventions for PPS.

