The web-based program will be offered after the meeting with the psychologist and will consist of 10 manualized modules at 1-week intervals. Participants will be instructed to complete each module and to continue to integrate the content into their daily lives during the following weeks. The modules will include psychoeducation and experiential exercises and training aimed at improving wellbeing and psychological flexibility following the contextual behavioral approach to wellbeing (Table 2). All the modules will include experiential exercises. The participants will receive weekly written feedback on each module from psychologists, nurses, and a social worker who will act as therapists in the study. These therapists are employed by the Hospital District of Helsinki and Uusimaa and are trained in providing web-based interventions to various populations. In addition to written feedback, the therapists will call all the participants and give them instructions for registering and using the program. The participants can contact the therapist *via* the web-based program at any time and all messages will be replied to within 1 week. Additional automatic reminders will be sent if a participant has not been active. If necessary, the therapists will call participants who have discontinued the program. They can track progress and read the answers to all the program’s written exercises and tasks.

**Table 2 tab2:** Summary of contents of the web-based program in use from June 2021 onward.

Module	Theme and aims	Examples of exercises
1. Module	**Introduction and bodily symptoms.** A brief introduction to the program including practical information. Information on central nervous system functioning.	“Ready for change” questionnaire, progressive relaxation^a^ ***Homework*****:** Progressive relaxation exercise begins ^a^
2. Module	**Stress system.** The aim is to get information about the stress system and identify the factors and acts that increase or decrease wellbeing.	“Tug-of-war” metaphor, “Mindful breathing” exercise ***Homework*****:** progressive relaxation exercise continues^a^, “Mindful breathing” exercise, taking action to increase wellbeing

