### Randomization and blinding

2.10.

If the inclusion criteria are met, the participants are allocated to the control group or treatment group by a pre-programmed, SPSS software-generated random allocation sequence modified from Arifin (2012). The allocation sequence will be carried out and concealed by a researcher who is not otherwise involved in the FIOH trial. The allocation ratio will be 1:1 so that the number of participants with either indoor air-related persistent symptomatology or with chronic fatigue will be balanced in both groups. After the clinical interview, the eligible participants will be assigned to the next study arm. Once the participants have been randomized, the SS or KK will contact them by telephone and email to inform them of their allocation. At the same time, the participants will receive the educational leaflet by email.

As this study compares an eHealth intervention with TAU, it is not possible to blind the study participants. However, the therapists provide support for all the patients referred to a web-based intervention program and are not explicitly informed if a patient is referred from the study. To wit, study participants and patients using the web-based program for other medical reasons are treated similarly independently of the referring unit. The data analysts will be blinded to the intervention arms.

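### Two of the acceptability sources, the late Working Alliance Inventory and the 12-month volunteer interview, are set so that participants who stop the programme are likely to be under-represented

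*Protocol article*

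**What the plan says.** Section 1.1 (Objectives) says adherence and response to treatment will be explored to "increase our understanding of the acceptability of the interventions for PPS". The Introduction names withdrawal from treatment as a known unwanted effect in this field and describes acceptability as low. The Discussion promises new information on acceptance.

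Table 4 (Section 2.8) has a block on satisfaction, adverse effects and usage with five rows:

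- **WAI:** marked at 0 W, 6 W and 14 W. Its footnote says that in the eHealth arm "the participants fill in the Working Alliance Inventory (WAI) for4 weeks from the beginning of the web-based program and after the last module".
- **Treatment satisfaction:** marked at 0 W, 6 W and 14 W.
- **"Interview of treatment acceptance":** one mark, at 12 months. The text of Section 2.8 describes the sample: "A random sample of volunteer participants will be interviewed at the end of the trial considering the treatment to gather qualitative data".
- **Engagement:** logins, time, modules and exercises done; no time column marked.
- **"Reasons for discontinuing":** no time column marked.

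The table legend counts 14 W from the 0 W questionnaire and 6 W from the start of the eHealth intervention. On contact with people who stop, Section 2.6 says: "If necessary, the therapists will call participants who have discontinued the program". Section 2.10 adds that these therapists "are not explicitly informed if a patient is referred from the study".

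**The concern.** When acceptability is the question, people who stop the programme are the most informative participants. A source that depends on reaching the last module, or on volunteering at the end of a 12-month follow-up, will tend to hear from those who finished and stayed. Alliance late in the programme, and the qualitative account of how the treatment was received, could then mainly describe completers.

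The WAI also has a plain internal conflict: one instrument has two schedules. Whichever is followed, someone reading the article cannot tell which participants should have a late score. The missing-data pattern for that score therefore cannot be interpreted.

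**Working it through.** The plan states no figure on this point, so the check sets the provisions side by side.

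**1. WAI: row against footnote.** The garbled footnote is read here as 4 weeks into the web programme.

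| | Row in Table 4 | Footnote |
|---|---|---|
| Occasions | three: 0 W, 6 W, 14 W | two: 4 weeks into the web programme; after the last module |
| Clock for the late score | calendar, from the 0 W questionnaire | completion of module 10 |
| Participant who stops at module 4 | late score due at 14 W | no late score ever due |

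The two can be brought close for a participant who runs on schedule. The intervention opens with two video meetings before the web programme. If these take 6 − 4 = 2 weeks, 6 W and the 4-week point coincide. If module 1 opens 14 − 10 = 4 weeks after 0 W, the end of ten weekly modules falls at 14 W. The rules separate for anyone who stops. The number of occasions also differs. The legend places 0 W after the recruitment interview, so that mark needs explaining too, since the alliance with a psychologist or therapist comes later.

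**2. Size of the WAI gap under the footnote.** Let d be the share of starters who stop before the last module. The late score is missing by design for d under the footnote and for 0 under the row. The documents give no d. As an assumption, take d from 20% to 40%. The lower value borrows the follow-up attrition ceiling in Section 2.12, which is not the same thing as stopping the programme. With the 62 per arm from the power calculation:

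- d = 20%: 0.20 × 62 = 12.4, about 12 participants
- d = 40%: 0.40 × 62 = 24.8, about 25 participants

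**3. Interview.** Twelve months is 52 weeks after 0 W, so the interview falls 52 − 14 = 38 weeks after the 14 W questionnaire. Random sampling from volunteers does not undo the selection involved in volunteering. People who stopped are not barred, but nothing secures their inclusion. Programme status will be known: module completion is logged, and Section 2.13 plans a separate analysis of those who complete the programme.

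**4. The remaining sources.** Engagement is recorded up to the point of stopping. Satisfaction at 14 W does not depend on modules done. The discontinuation-reasons row can only concern people who stop. None of the three requires completion.

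**The case against.** The strongest reply is that the plan does collect evidence on people who stop: reasons for discontinuing, engagement logs and calendar-timed satisfaction. Section 1.1 ties acceptability to adherence and response, not to the interview or the alliance score. This stands, and it rules out a stronger reading that a reader might infer, namely that people who stop disappear from the evidence on why people stop.

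A reader might also infer that reasons are gathered only through the therapists' discretionary call, and so outside the trial. The documents do not say that. Section 2.6 describes the call as programme support, and nothing prevents the trial team from asking in its own questionnaires. The reasons row has no time or method, but an article may leave that to the full protocol.

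Nor can a percentage be put on any overstatement of acceptability. The interviews are meant to be qualitative, no acceptability proportion is planned from them, and every input to such a figure would be invented.

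It is also fair that interviews need consent, so some volunteering is unavoidable; that the interview is not restricted to completers; and that the 4-week WAI can reach those who stop later. These points reduce the concern. They do not resolve the conflict between row and footnote, and they do not secure the inclusion of people who stopped in the interview sample.

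**Conclusion.** The point holds in a limited form. The WAI schedule contradicts itself, and under the footnote rule everyone who stops early lacks a late alliance score. The acceptance interview draws on volunteers at 12 months with no provision for people who stopped, although acceptability is an aim and withdrawal a recognised problem. That such people will be under-represented among the interviewed volunteers is a likely consequence, not something the documents state.

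The effect is confined to these two sources. It does not reach the primary 15D analysis, the satisfaction measure, the engagement data or the listed reasons for discontinuing. The counts of about 12 to 25 participants rest on assumed stopping rates and on the footnote being the rule that is followed; if the row governs, that gap is zero by design.

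**What to change.** 1. Reconcile the WAI row with its footnote, including the 0 W mark. Take the late WAI at the existing 14 W questionnaire from every intervention participant who started the programme, whatever the number of modules completed. The cost is a corrected table entry, since the row already marks 14 W.

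2. Keep the end-of-trial interview, but stratify invitations by programme status: stopped before module 10, or completed. Report the numbers invited and interviewed in each stratum. The number of interviews can stay similar. The small downside is that people who stopped may be harder to recruit.

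Moving the interview to about 14 weeks is not recommended as part of this fix. It would shorten the recall interval, but it would add a trial contact in one arm before the 6- and 12-month assessments, in an unblinded trial with a self-reported primary outcome. A separate new item on reasons for stopping is not needed either, because it would largely repeat a row already listed.
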